##### Glucose exposure metrics

Between group differences in AUC for blood glucose during periods when blood glucose levels reach 10–13.9 mmol/L and 13.9–22.2 mmol/L.

Between group differences in AUC for blood glucose during periods when blood glucose levels reach 3–3.9 mmol/L and < 3 mmol/L.

Between group differences in mean daytime blood glucose levels.

Between group differences in mean nocturnal blood glucose levels.

Between group differences in eHBA_1c_.

##### Glycemic variability metrics

Between group differences in SD of 24-h blood glucose values.

Between group differences in the SD of daytime blood glucose values.

Between group differences in SD of nocturnal blood glucose values.

Between group differences of MAGE (mean amplitude of glycemic excursions).

Between group difference in glucose variability measured by the coefficient of variation (CV).

##### Other metrics

Between group differences in number of hypoglycemic events in total and divided into levels (3–3.9 mmol/L, < 3 mmol/L or a need for third party assistance to restore blood glucose).

and nighttime/daytime.

Between group differences in number of hyperglycemic events in total and divided into levels and nighttime/daytime.

Hypo- and hyperglycemic events are defined as at least 15 min spent in the specific range and each event must be at least 30 min apart. Nighttime is defined as midnight – 6. am [11].

#### Other secondary outcomes

1) Number of patients in each group that reach a daily mean glucose level of 6–12 mmol/L during treatment for at least 7 out of the first 14 days of treatment. Outcome measure: CGM and SMBG mean glucose levels. SMBG outcome measure: Mean plasma glucose difference between the empagliflozin and NPH insulin group. Patients will both fill out a diary and the data will also be downloaded directly from the patients glucometers. A minimum of 15 complete 4-point profiles pr. patient will be needed (out of 30) for the patient to be included in this secondary endpoint statistical analysis. The capillary glucoses are to be taken: 1) morning fasting 2) preprandial noon 3) preprandial dinner 4) bedtime.

2) Number of events of mild hypoglycaemia and severe hypoglycaemia (need for third party assistance to restore blood glucose).

3) Quality of life: Outcome measures: PRO from questionnaires including VAS-rating, interviews and information from electronic patient record.

#### Exploratory objectives

To compare the effect of empagliflozin versus NPH insulin on:
The Karnofsky performance status scoreOutcome measure: Change from baseline to 14 and 30 days in Karnofsky Performance status score [12].Health-related quality of life from the short SF-36 Health Survey, an 36-item validated patient-reported survey of patient health [24]. Outcome measure: Change from Baseline to 30 days in the short SF-36 questionnaire summary physical score (PCS) and summary mental score (MCS).Changes from Baseline in Visual Analogue Scale (VAS), interindividual and in between the two groups. The VAS has been extensively used in the evaluation of health-related quality of life (HRQL). The VAS is used to monitor patient-reported current health on a scale from 0 to 100 [25].Fructosamine (FA) levels at day 1, 14 and 30. Outcome measure: Differences in FA changes between the 2 groups from laboratory results at day 1, 14 and 30. FA was chosen as it reflects the mean glycemic control in a shorter time (2–3 weeks) compared with glycated hemoglobin (HbA_1C_). HbA_1c_ and FA levels are highly correlated. Because FA reflects glycated S-proteins, results from patients with albumin out of the normal range cannot be included in the analysis [26].Between group differences in HbA_1c_ changes based on their baseline HbA_1c_ to 30 days.Effect on systolic BP. Outcome measure: Change in systolic BP from baseline.Bodyweight. Outcome measure: change in bodyweight from baseline.

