**Table Tab1:**
[figure not shown]
Table 1.

The investigator will prior to visit 1 assess eligibility from the laboratory results (eGFR and fluid balance). If not eligible, patients will not be allowed to continue to visit 1 (screen failures).

Visit 1: general physical examination, vital signs (blood pressure and pulse), concomitant medication, including dose of glucocorticoid, recording of AE’s or SAE’s since last visit if not on same day as enrolment, randomization in REDcap®, dispensing of IP’s. Instructions by project nurse in glucose measurements, study drug use, reporting to research staff, CGM-sensor is attached. Short SF-36 Questionnaire in REDcap® (The short SF-36 Health Survey is a 36-item validated patient-reported survey of patient health), Visual Analogue Rate Scale of Health-related quality of life (Monitoring of patient-reported current health on a scale from 0 to 100), Charlson comorbidity score, Karnofsky Performance status.

Visit 2 (telephone visit - 3 days after visit 1): Instructions by project nurse in glucose measurements and study drug use are repeated, recording of AE’s or SAE’s since last visit, Short SF-36 Questionnaire in REDcap®, VAS, glucocorticoid dose, study drug dose.

Visit 3 (7 days after visit 1): Removal of CGM, attachment of new CGM, recording of AE’s or SAE’s since last visit, Short SF-36 Questionnaire in REDcap®, VAS, glucocorticoid dose, study drug dose.

Visit 4 (14 days after visit 1): Removal of CGM. Gathering data about: Glucose measurements, symptoms of hyperglycaemia and side-effects of medication, episodes of severe hypoglycaemia, number of contacts between patient and general practitioner due to diabetes related problems, other hospital physicians and any admissions to hospital. General physical examination and vital signs, laboratory tests, recording of AE’s or SAE’s since last visit, Short SF-36 Questionnaire in REDcap®, VAS, glucocorticoid dose, study drug dose.

Visit 5 (Telephone visit - 21 days after visit 1): As visit 2.

Visit 6 (30 days after visit 1): Recording of AE’s or SAE’s since last visit, glucocorticoid dose, study drug dose. Laboratory tests are repeated, finger prick ketones, future biobank sample collection (plasma, serum, whole blood), vital signs, Short SF-36 Questionnaire in REDcap®, VAS-scale, Charlson comorbidity score, Karnofsky Performance status.

Visit 7 (safety follow-up - 7 days after trial medication is stopped).

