### Statistics

#### Power

A total of 74 patients should be included to allow randomization of approximately 37 patients in each arm, and for at least 29 patients to complete 30 days of treatment per arm, with alpha set to 0.05 and beta 0.90. It is estimated that a total of 58 completing patients can provide 90% power to detect a significant difference (two-tailed p-value ≤0.05) between the two treatments in reduction of plasma glucose, if there is a true difference of 2 mmol/L (non-inferiority limit) with a standard deviation (SD) for plasma glucose of 2.6 mmol/L. In our own recent study, which included 1131 blood glucose measurements in patients with newly diagnosed GIDM, we found an SD of 4.2 mmol/L [13]. In another study with 21 patients that developed GIDM after prednisolone, an SD of 1 mmol/L was calculated [28]. Thus, because the true SD for glucose for GIDM is not known, the SD used for the power calculation was pragmatically calculated as a mean from the 2 studies.

It is expected that up to 16 patients (25%) may leave the study prematurely, thus a total minimum of 74 patients will be included and at least 58 complete the study.

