#### Secondary analysis

Continuous variables analysis will be done using a T-test. For categorical outcomes a Chi-square test will be used.

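### SF-36 PCS and MCS are cut to one baseline-to-day-30 change, and the only test named is a t-test; a baseline-adjusted repeated-measures model would be more precise at almost no cost (minor)

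*Protocol article*

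**What the plan says.** **Collection.** The protocol article's Visit procedures schedule both instruments at visits 1 to 6:

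- Visit 1 (day 0): SF-36 and "Visual Analogue Rate Scale of Health-related quality of life (Monitoring of patient-reported current health on a scale from 0 to 100").
- Visits 2, 3 and 4 (days 3, 7 and 14): each list contains "Short SF-36 Questionnaire in REDcap®, VAS, glucocorticoid dose, study drug dose".
- Visit 5 (day 21), by reference: "Visit 5 (Telephone visit - 21 days after visit 1): As visit 2".
- Visit 6 (day 30): SF-36 and VAS again.

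This gives one baseline and five post-baseline scores per instrument.

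**Outcome.** Exploratory objectives fix the SF-36 outcome: "Outcome measure: Change from Baseline to 30 days in the short SF-36 questionnaire summary physical score (PCS) and summary mental score (MCS"). The VAS entry there names no time point: "Changes from Baseline in Visual Analogue Scale (VAS), interindividual and in between the two groups". Other secondary outcomes also include "Quality of life: Outcome measures: PRO from questionnaires including VAS-rating".

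**Analysis.** Secondary analysis states: "Continuous variables analysis will be done using a T-test". No baseline-adjusted or repeated-measures model is named for these scores.

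**Population and attrition.** The Statistical analysis plan section names an intention-to-treat analysis of all randomised subjects alongside a per-protocol analysis, and defers a detailed plan. The Power section gives 74 randomised and 58 completing: "It is expected that up to 16 patients (25%) may leave the study prematurely".

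**The concern.** A t-test on the day-30 change has two weaknesses.

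First, subtracting the baseline gives it a fixed weight of one. Unless the baseline-to-day-30 correlation is close to 1, that overcorrects and adds noise. Estimating the weight by regression is more precise.

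Second, without some method for missing scores, the t-test can use only patients who have a day-30 score. A patient who leaves after the day-21 visit has four post-baseline scores, and none of them enters. Such patients belong to the stated intention-to-treat set. If leaving depends on how the patient was already scoring, the difference among those with a day-30 score may be biased.

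At stake is the quality-of-life comparison, which is a secondary outcome in general terms and exploratory as far as PCS and MCS are named. Non-inferiority on mean CGM glucose does not depend on it.

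**Working it through.** **Inputs from the article.** 74 randomised, 37 per arm; 58 completing, 29 per arm; six visits at days 0, 3, 7, 14, 21 and 30.

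**The article's own attrition figure.** 74 − 58 = 16, or 8 per arm. 16/74 = 21.6%, not the 25% printed beside it; the calculation below uses the counts. The article gives no sample size for SF-36 or VAS, so there is no precision figure to reproduce for them.

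**Assumptions, not in the article.** Baseline-to-day-30 correlation ρ of 0.3, 0.5 or 0.7; equal variance σ² at all visits.

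**Step 1: change score against baseline adjustment, same 29 completers per arm.**

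- Change-score t-test: variance of the difference = (2/29) × 2(1 − ρ)σ².
- Baseline-adjusted (ANCOVA): (2/29) × (1 − ρ²)σ².
- Ratio = (1 − ρ²) / [2(1 − ρ)] = (1 + ρ)/2.

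The ANCOVA formula ignores the small cost of estimating the slope.

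| ρ | variance ratio | variance saved | SE ratio | equivalent completers per arm with the t-test |
|---|---|---|---|---|
| 0.3 | 0.65 | 35% | 0.81 | 29/0.65 ≈ 45 |
| 0.5 | 0.75 | 25% | 0.87 | 29/0.75 ≈ 39 |
| 0.7 | 0.85 | 15% | 0.92 | 29/0.85 ≈ 34 |

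At ρ = 0.5 the t-test has SE = √(2/29) = 0.263 SD, and ANCOVA has 0.263 × 0.866 = 0.227 SD.

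**Step 2: add the interim visits and the early leavers.** The model is a likelihood-based repeated-measures model with a common baseline mean. It uses all 37 per arm, with the 8 leavers per arm spread evenly over the five stages before day 30, so some give a baseline score only. Three correlation patterns were used: compound symmetry, exponential decay over time, and an equal mix of the two.

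| ρ | SE against the t-test | SE against ANCOVA |
|---|---|---|
| 0.3 | 0.79–0.80 | 0.982–0.991 |
| 0.5 | 0.84–0.85 | 0.975–0.984 |
| 0.7 | 0.89–0.90 | 0.969–0.977 |

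If instead every leaver gives at least one post-baseline score (2 per arm at each of four stages), SE against ANCOVA runs from 0.989 to 0.963. With leaving spread evenly, the extra data therefore take about a further 1–4% off the SE. At ρ = 0.5 with compound symmetry and this second pattern, the SE goes from 0.263 (t-test) to 0.227 (ANCOVA) to 0.223 SD (repeated measures). That is a drop of 0.036 from the covariate and 0.004 from everything else.

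**Step 3: what the extra data do for bias.** A t-test on patients with a day-30 score needs leaving to be unrelated to the change within each arm. The repeated-measures model allows leaving to depend on scores already observed. That is a weaker assumption, but the model does not cure leaving that depends on unobserved scores. The article gives no figure from which the bias could be sized.

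**The case against.** **The t-test is not tied to SF-36 by name.** SF-36 PCS and MCS stand under exploratory objectives, and the t-test sentence stands under Secondary analysis. This is fair: the link runs through the secondary quality-of-life item, which refers to questionnaires and VAS without naming SF-36. It remains the only test named for continuous outcomes beyond the primary.

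**Handling of leavers may be settled in the fuller plan.** The article announces one and names all randomised subjects as the intention-to-treat set. This also stands. The absence of a missing-data method in a condensed article is not the point here; the point is the stated combination of a single change score and a t-test.

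**A day-30 endpoint is legitimate.** Agreed. The fix keeps day 30 as the reported contrast. For VAS the time point is open, so the cut to day 30 applies only to SF-36.

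A reader might also infer three stronger things:

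- *That the comparison is no longer a randomised one.* The documents do not show this. No bias is demonstrated or quantified, the intention-to-treat set is all randomised subjects, and patients who stop study drug for normoglycaemia after glucocorticoids end keep their visits.
- *That the precision loss comes from the unused visits and the lost leavers.* Steps 1 and 2 show that most of it comes from not adjusting for baseline.
- *That 16 patients will be lost.* The article gives 16 as an upper figure.

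**Conclusion.** The point holds as a minor one. Under assumed correlations of 0.3 to 0.7 and equal variances, the stated approach gives up 35% to 15% of variance that baseline adjustment alone would recover, on the same patients. The interim scores and early leavers add about 1–4% in standard error when leaving is spread evenly. Their main value is to keep patients without a day-30 score in the comparison, which lowers possible bias if leaving depends on earlier scores. Whether such bias would arise, and in which direction, cannot be told from the article. The outcomes concerned are secondary or exploratory, and the primary conclusion is untouched.

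**What to change.** Replace the change-score t-test for SF-36 PCS, SF-36 MCS and VAS with a baseline-adjusted repeated-measures model:

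- use all scheduled post-baseline scores (days 3, 7, 14, 21 and 30) from all randomised patients who have any;
- include baseline score, treatment, visit, treatment-by-visit and the glucocorticoid-dose stratum used at randomisation;
- report the day-30 difference between arms with its 95% CI, which also gives VAS the time point it lacks;
- report deaths by arm beside it, because a missing score after death is not the same as one missed by a living patient.

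The cost is analysis wording and a missing-at-random assumption that should be stated openly. No new data, visits or patients are needed. The article says that the detailed analysis plan is to be agreed before the randomisation code is added to the cleaned data, so the change can be made there.

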### Patient selection

The target population is hospitalized patients, or equal to being hospitalized as judged by the local investigator, with newly onset GIDM, defined by a fasting plasma glucose of above 7 mmol/L or a plasma glucose of 11.1 mmol/L or more at two different times or one increased glucose value AND hyperglycaemic symptoms after receiving glucocorticoid in a dose equivalent to > 20 mg prednisolone. The participant must not have had any type of diabetes before, or any pancreatic diseases. It is permitted that the participant receive treatment with p.n. insulin prior to the screening procedure (for up to a week), if it is estimated that the effect has worn off – e.g. if a patient has received a dose of p.n. insulin the night before the screening procedure is done.

Potential participants will be recruited by trained diabetes nurses, which are part of diabetes service teams in the participating hospitals, that are already in contact with patients with new-onset GIDM. Patients will be asked if they are interested in information about the trial, and if so, they will be informed in accordance with the Danish Regional Committee on Biomedical Research and Ethics. If the patient agrees to participate and signs the required forms, the project nurse will be contacted, and he or she will then perform the screening procedure, and if enrolled also the randomization in REDcap® (a web-based electronic CRF).

The study population is expected to suffer from a wide range of underlying diseases as patients will be screened from multiple centres and departments. The participants must have an eGFR of 60 ml/min/1.73m^2^ or above as the glucose-lowering effect of an SGLT2 inhibitor has been shown to be impaired with lower eGFRs [23]. If the investigator estimates, that the patient is in a state where the most recent eGFR is unreliable (acute kidney injury, dehydration, other), the patient cannot be included.

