### Visit procedures

Patients are seen in the hospital setting at 5 University Hospitals in Copenhagen, Denmark for visit 0–7 see Fig. 2 and Table 1. If not hospitalized, patients will be seen at the out-patient clinics at the abovementioned locations. Prior to any protocol-related procedures written informed consent is obtained. The patient is screened for in- and exclusion criteria at visit 0 and information about demography, medical and surgical history, family history of type 1 and 2 diabetes mellitus, current medication, indication for glucocorticoid treatment and dose of glucocorticoid, date of diagnosis of GIDM, vital signs: weight, height, blood pressure, pulse, general physical examination, volume status (lung auscultation and peripheral oedema examination (pitting) and weight), laboratory tests: Haemoglobin, fructosamine, HbA_1c_, plasma glucose, C-peptide, leukocytes with differential count, CRP, platelet count, iron, transferrin, MCV, reticulocytes, albumin, ALAT, ASAT, alkaline phosphatase, LDH, bilirubin, calcium-ion, lipids, creatinine, potassium, sodium, urea. Finger prick ketones, genetic research material collection for future biobank (plasma, serum, whole blood), pregnancy test in women of child-bearing potential with a standard dip-stick and urine test (signs of urinary tract infection).

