#### Safety objectives

To evaluate the safety and tolerability of empagliflozin compared with NPH insulin in treating GIDM. Outcome measures: SAEs. Discontinuation of investigational product (IP) due to adverse events. Changes in clinical chemistry/hematology parameters including finger prick ketones. AEs of interest (urogenital infections, volume depletion, diabetic ketoacidosis (DKA), HHS, hypoglycemic events and other AEs needing any treatment. Number of contacts between patient and general practitioner due to diabetes-related problems, and any admissions to hospital.

Percentage in each group that needing rescue medication due to hyperglycaemia. Outcome measure: Interviews and SP. Dose of sliding scale needed.

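### The albumin exclusion for the exploratory fructosamine outcome is not limited to baseline albumin, so it allows patients to be selected on a value measured after randomisation

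*Protocol article*

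**What the plan says.** Under Exploratory objectives, fructosamine (FA) is chosen because it reflects glycaemia over two to three weeks, a shorter window than HbA1c. The outcome is "Differences in FA changes between the 2 groups from laboratory results at day 1, 14 and 30". The restriction follows, with its reason and a citation: "Because FA reflects glycated S-proteins", "results from patients with albumin out of the normal range cannot be included in the analysis".

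Visit procedures puts albumin in the visit 0 panel ("MCV, reticulocytes, albumin, ALAT, ASAT, alkaline phosphatase"), before randomisation at visit 1. At visit 4 (day 14) the list reads "General physical examination and vital signs, laboratory tests, recording of AE’s or SAE’s since last visit". At visit 6 (day 30) it reads "Laboratory tests are repeated, finger prick ketones". Albumin is not named again at either visit, and the visit table is not reproduced in the text available.

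The Statistical analysis plan section promises an intention-to-treat analysis defined as all randomised subjects, a per-protocol analysis, and a description of incomplete data with reasons.

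**The concern.** The rule decides by a laboratory value who is analysed, and it does not fix when that value is taken. The outcome spans three time points, two of them after treatment has started. A reader applying the rule could drop a patient because of a day 14 or day 30 albumin. The groups compared would then be defined partly by something that happened after randomisation.

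Three things are at stake for this outcome: precision, the protection that randomisation gives if treatment moves albumin, and consistency with the all-randomised analysis. Patient selection gives some reason to expect that exclusions will occur: "The study population is expected to suffer from a wide range of underlying diseases as patients will be screened from multiple centres and departments". Safety objectives lists volume depletion among the events to be watched: "AEs of interest (urogenital infections, volume depletion, diabetic ketoacidosis (DKA), HHS, hypoglycemic events and other AEs needing any treatment". Loss of plasma volume is one conceivable route by which treatment could move albumin, but the article does not make that link.

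**Working it through.** The article gives no sample size, standard deviation or exclusion rate for fructosamine, so there is no stated figure to reproduce. The check has three parts.

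**1. Timing, from the text.** Visit 0 albumin is measured before randomisation at visit 1. Laboratory tests recur at days 14 and 30. The exclusion names no visit. Both readings, baseline only or any visit, are therefore open, and the second selects on a post-randomisation value. This assumes that the repeated laboratory tests include albumin.

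**2. Precision.** Inputs: 58 completers, 29 per arm (Power section). The excluded share f is assumed, equal in both arms.

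- Patients remaining = 58 × (1 − f)
- Widening of the confidence interval = 1/√(1 − f)
- Difference detectable with 80% power at two-sided 0.05, in SD units = (1.960 + 0.842) × √(2/n), with n = 29 × (1 − f) per arm

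| Assumed f | Remaining of 58 | Per arm | Widening | Detectable difference (SD) |
|---|---|---|---|---|
| 0% | 58 | 29 | 1.00 | 0.74 |
| 20% | 46.4 | 23.2 | 1.12 | 0.82 |
| 40% | 34.8 | 17.4 | 1.29 | 0.95 |
| 60% | 23.2 | 11.6 | 1.58 | 1.16 |

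**3. Bias when there is no true effect on fructosamine.** Take albumin and fructosamine change as standard normal with correlation ρ, and exclude patients whose albumin is below a cut-off c. For illustration only the low side is excluded. Suppose treatment raises on-treatment albumin by s SD in one arm.

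- *Baseline albumin decides.* Treatment cannot affect a value taken before it starts, so selection is the same in both arms and the expected bias is 0. A simulation with one million patients per arm gave values within 0.003 SD of zero.
- *On-treatment albumin decides.* Bias = ρ × [λ(c − s) − λ(c)], where λ(x) = φ(x)/(1 − Φ(x)). If s = 0, the bias is 0.

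For a 40% exclusion rate in the unaffected arm, c = −0.253 and λ(c) = 0.644. With s = 0.5, λ(c − s) = 0.388. With ρ = 0.5 the bias is 0.5 × (0.388 − 0.644) = −0.128 SD.

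| Excluded, unaffected arm | s | Excluded, shifted arm | Bias, ρ = 0.3 | Bias, ρ = 0.5 |
|---|---|---|---|---|
| 20% | 0.3 | 12.7% | −0.03 | −0.06 |
| 20% | 0.5 | 9.0% | −0.05 | −0.09 |
| 40% | 0.3 | 29.0% | −0.05 | −0.08 |
| 40% | 0.5 | 22.6% | −0.08 | −0.13 |

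The simulation agreed with each entry to within 0.003 SD. The sign follows from the signs assumed for s and ρ. All values of f, s and ρ are assumptions.

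**The case against.** The strongest reply is that this is a prespecified assay-validity restriction with a stated reason and a citation. A marker built on glycated serum proteins may not be interpretable when albumin is abnormal, and discarding such results may be the honest course. That stands as a reason for having a restriction. It does not explain why the restriction is left open to post-randomisation values.

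A second reply is that the deciding visit, the choice between dropping a sample or a patient, and sensitivity analyses belong in the fuller analysis plan, which is not shown. That is fair for sample versus patient and for the choice of sensitivity analyses. The exclusion itself, however, is stated affirmatively in the article and without a time limit, so the point concerns what is written.

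Some stronger readings are tempting, and the article does not support them:

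- A reader might infer that the rule destroys the randomised comparison. If baseline albumin decides, the remaining patients are still a randomised comparison, only smaller and less general.
- A reader might infer a large loss from an acutely ill population. The article describes patients who are hospitalised or equivalent, requires an eGFR of at least 60, and gives no rate of abnormal albumin.
- A reader might infer that fructosamine is the only blood-based measure of glycaemia with a suitable window. Other secondary outcomes includes capillary self-monitoring in four-point profiles over 30 days, and the primary outcome is 14-day CGM.
- A reader might infer that dividing fructosamine by albumin should replace the restriction. That albumin is measured does not make the ratio valid, and nothing in the article validates it.

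**Conclusion.** The point holds as a minor one. The restriction is written so that post-randomisation albumin can decide who is analysed, and for this outcome it departs from the all-randomised analysis that the same article plans. The precision cost is unknown. Over an assumed exclusion of 20% to 60%, intervals widen by 1.12 to 1.58. Bias is not shown: it requires both that on-treatment albumin decides and that treatment shifts albumin. Under assumed shifts of 0.3 to 0.5 SD and correlations of 0.3 to 0.5 it would be about 0.03 to 0.13 SD, with unequal exclusions between arms as the visible sign. Fructosamine is one of several exploratory outcomes, and the non-inferiority conclusion on CGM mean glucose does not depend on it.

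**What to change.** Before the randomisation code is joined to the cleaned data, amend the wording for this outcome:

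1. Define the normal-albumin restriction on baseline (visit 0) albumin only, so that no patient is removed because of a later value.
2. Compare follow-up fructosamine between arms with adjustment for baseline fructosamine.
3. Report the number excluded by arm.
4. Add a sensitivity analysis of all randomised patients with a fructosamine sample, with albumin as a covariate or with albumin-corrected fructosamine, presented beside the restricted analysis.

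The cost is analysis wording only. No visit or assay is added, provided that albumin is among the laboratory tests repeated at days 14 and 30. Otherwise the sensitivity analysis can use baseline albumin alone.

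There are two downsides. Some follow-up samples taken while albumin is abnormal will be kept, which weakens the assay-validity protection that the authors wanted. The all-patient analysis also rests on an albumin adjustment that the article does not validate, so it should supplement the restricted analysis and not replace it.
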